#### Secondary outcome analysis

2.4.9

The secondary study parameters (back pain, leg pain, self‐perceived recovery, health‐related quality of life, and functional status) will be analysed in the same way as the primary study parameter (i.e., surgery). However, for continuous outcomes, we will use a linear mixed model with the same multilevel structure.

#### Economic evaluation

2.4.10

An economic evaluation will be performed from a societal and a health care perspective. When the societal perspective is applied, all costs and consequences relevant to the intervention will be taken into account irrespective of whom pays or benefits, whereas only those accruing to the formal Dutch health care sector will be considered when the health care perspective is applied (Hakkaart‐van Roijen, van der Linden, Bouwmans, Kanters, & Tan, 2015; Brouwer, van Exel, Baltussen, & Rutten, 2006).

The economic evaluation will be performed in accordance with the intention‐to‐treat principle and in terms of quality‐adjusted life years as well as the primary outcome proportion of LRS patients undergoing lumbar disc surgery during 12‐month follow‐up. Missing data will be imputed using multiple imputations by chained equations. The imputation model will be constructed in accordance with the recommendations of White, Royston, and Wood (2011). Imputed datasets will be analysed as specified below, after which pooled estimates will be estimated using Rubin's rules (White et al., 2011). Incremental cost‐effectiveness ratios will be calculated by dividing the difference in costs by that in effects. In order to account for the possible clustering of data, analyses will be performed using linear mixed models (Gomes et al., 2012). Accounting for the possible clustering of data (e.g., at the hospital level) is very important, as most economic evaluations fail to do so, whereas ignoring the possible clustering of data might lead to inaccurate levels of uncertainty and inaccurate point estimates (Gomes et al., 2012). Bootstrapping techniques will be used to estimate the uncertainty surrounding the cost‐effectiveness estimates. Uncertainty will be shown by plotting cost‐effect pairs on cost‐effectiveness planes and by constructing cost‐effectiveness acceptability curves (Black, 1990; Drummond, Sculpher, Torrance, O'Brien, & Stoddart, 2005; Fenwick, O'Brien, & Briggs, 2004). Cost‐effectiveness acceptability curves indicate the probability of an intervention being cost‐effective compared with a control for a range of ceiling ratios (i.e., the maximum amount of money decision makers are willing to pay per unit of effect gained).

Various one‐way sensitivity analyses will be performed to test the robustness of the study results (e.g., complete‐case analysis and per‐protocol analysis).

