#### Secondary outcomes measures

2.3.3

In line with the core outcome set for clinical research and clinical practice (Chiarotto et al., 2018), secondary study parameters include back and leg pain, physical functioning, and health‐related quality of life. Additionally, we will measure self‐perceived recovery, patient satisfaction (single question), and pain location (pain mannequin). Measurements will take place at baseline, 2, 4, 6, 9, and 12 months after randomization and administered through online questionnaires. An additional pain intensity measurement will be carried out at 4 weeks after randomization. The rationale is that, especially leg pain, will improve in the combination group. Complications will be noted in a case report form. Societal and health care costs will be estimated for economic evaluation using resource use data, collected through online questionnaires at baseline, 2, 4, 6, 9, and 12 months after randomization.

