##### Health‐related quality of life (EQ‐5D‐5L and SF‐12)

The EQ‐5D‐5L is a quality of life scale that is responsive for chronic low back pain patients (Soer, Reneman, Speijer, Coppes, & Vroomen, 2012). The EQ‐5D‐5L has five health dimensions: mobility, self‐care, daily activities, pain/discomfort, and anxiety/depression. Within each dimension, the patients can self‐rate their level of severity; no, slight, moderate, severe problems, unable to perform, or do the task (Versteegh et al., 2016). For the economic evaluation, the patients' EQ‐5D‐5L health states will be converted into utility scores ranging from 0 (“death”) to 1 (“optimal health”) using the Dutch tariff (Versteegh et al., 2016).

The SF‐12 is a shorter version of the SF‐36 health‐related quality‐of‐life questionnaire. The SF‐12 has been proven to be a reliable and valid questionnaire for low back pain (Xuemei et al., 2003). The questionnaire relates to the analysis of the general functional status of patients. It consists of 12 questions from the following eight domains: (a) physical functioning, (b) physical role limitations, (c) emotional role imitations, (d) social functioning, (e) physical pain, (f) general mental health, (g) vitality, and (h) general health perception. These eight domains can be summarized into a physical and psychological main domain (Xuemei et al., 2003). For the economic evaluation, quality‐adjusted life years will be calculated by multiplying the patients' time spent in a certain health state by the respective utility value (i.e., area under the curve method).

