##### Societal and health care costs

Societal costs include costs of the intervention, other health care use, informal care, unpaid productivity losses, and costs due to absenteeism (i.e., sickness absence) and presenteeism (i.e., being less productive while being at work). Health care costs will only include costs accruing to the formal Dutch health care sector.

Intervention costs will be microcosted. For this purpose, information about the combination therapy will be gathered using a case report form, including information on patient classification, number of sessions, discharge, and referral to a network MDT or to the surgeon. All other cost categories will be measured using cost questionnaires administered at baseline 2, 4, 6, 9, and 12 months after randomization. Resource use will be valued in accordance with the Dutch manual of costing (Hakkaart‐van Roijen, Tan, & Bouwmans, 2010). See Table 1: overview of the data collection.

**Table 1 pri1796-tbl-0001:** Overview of the data collection

Outcome measures	Baseline	4 weeks	2 months	4 months	6 months	9 months	12 months
Prognostic factors							
Patient demographics and prognostic factors	X						
Primary outcome							
Surgery rate			X	X	X	X	X
Secondary outcomes							
Pain leg (NPRS)	X	X	X	X	X	X	X
Pain back (NPRS)	X	X	X	X	X	X	X
Health‐related quality of life (EQ‐5D‐5L and SF‐12)	X		X	X	X	X	X
RMDQ‐23	X		X	X	X	X	X
Self‐perceived recovery (GPE)			X	X	X	X	X
Societal and health care costs (cost questionnaires)	X		X	X	X	X	X
Patient satisfaction, complications, and pain location	X		X	X	X	X	X

Abbreviation: NPRS, numeric pain rating scale; RMDQ, Roland Morris Disability Questionnaires.

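### The QALY and cost models could adjust for baseline utility and baseline cost, both already collected, at almost no cost; section 2.4.10 names neither (an improvement, not an error)

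*Protocol article*

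**What the plan says.** All references are to the Protocol article.

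- **Data.** Section 2.3.3 says of the secondary outcomes, which include health-related quality of life: "Measurements will take place at baseline, 2, 4, 6, 9, and 12 months after randomization". Resource use is "collected through online questionnaires at baseline, 2, 4, 6, 9, and 12 months after randomization". Table 1 marks both at baseline.
- **QALY.** The EQ-5D-5L health states "will be converted into utility scores ranging from 0" (death) to 1 (optimal health) with the Dutch tariff, and QALYs follow by the "area under the curve method".
- **Economic model.** Section 2.4.10 gives possible clustering as the reason and says that "analyses will be performed using linear mixed models". Hospital is given as an example of the clustering level. The section also sets out multiple imputation, Rubin's rules, bootstrapping, cost-effectiveness planes, acceptability curves and sensitivity analyses (complete-case and per-protocol are the examples). No baseline term is named.
- **Adjustment elsewhere.** Section 2.4.8 allows the surgery analysis to be adjusted for unnamed prognostic characteristics where needed, and section 2.4.9 extends that approach to health-related quality of life. Section 2.4.10 refers to neither.
- **Randomization.** Section 2.4.1 stratifies on duration of complaints, with one list per hospital. Neither utility nor cost is balanced by design.

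**The concern.** Baseline utility enters the QALY in two ways. It is the first point on the curve, and it predicts the later points. When the arms differ at baseline by chance, an unadjusted QALY contrast includes part of that difference, and the variation that baseline explains stays in the error term. Adding baseline utility to the model deals with both. Multiple imputation and bootstrapping do not: the first fills in missing values, and the second describes the uncertainty of whichever estimator is chosen.

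Cost-effectiveness is half of the stated aim. The incremental QALY is the denominator of one of the two planned cost-effectiveness ratios and feeds its plane and acceptability curve. The sample size in section 2.4.6 was set for the surgery rate, so precision for QALYs is whatever 146 patients happen to give.

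**Working it through.** The plan gives no figure for QALY precision, so there is none to reproduce. The only number taken from its sample size is 146/2 = 73 per arm.

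**Inputs from the document.** Visits at 0, 2, 4, 6, 9 and 12 months; area under the curve; 1:1 allocation; 73 per arm.

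**Assumptions (not in the document).** Utility SD 0.20-0.30, equal at all visits; baseline-to-follow-up correlation r = 0.2-0.5; correlation between follow-up visits 0.6; trapezium rule; clustering and drop-out ignored.

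**Step 1, weights.** With time in years the trapezium weights are 0.083, 0.167, 0.167, 0.208, 0.250 and 0.125, which sum to 1. Baseline has weight 1/12 and the follow-up visits together 11/12.

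**Step 2, share of a baseline gap carried.** The slope of QALY on baseline utility is b = 1/12 + (11/12)r. At r = 0.2, b = 0.083 + 0.183 = 0.267. At r = 0.5, b = 0.083 + 0.458 = 0.542. For a gap of 0.05 this is 0.013 to 0.027 QALY, of which 0.05/12 = 0.0042 comes directly from the baseline point.

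**Step 3, size of a chance gap.** Its standard error is SD × √(2/73), which is 0.033 at SD 0.20 and 0.050 at SD 0.30. A gap of one standard error shifts the incremental QALY by 0.267 × 0.0331 = 0.0088 at the low end and 0.542 × 0.0497 = 0.0269 at the high end.

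**Step 4, precision.** The variance of the QALY is SD² × v. The squared follow-up weights sum to 0.1771, so

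v = (1/12)² + 2(1/12)(11/12)r + 0.6(11/12)² + 0.4 × 0.1771 = 0.582 + 0.153r.

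The correlation of QALY with baseline utility is ρ = b/√v, and adjustment multiplies the standard error by √(1 − ρ²). The last two columns use SD 0.25.

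| r | b | ρ | SE ratio | SE unadjusted | SE adjusted |
|---|---|---|---|---|---|
| 0.2 | 0.267 | 0.341 | 0.940 | 0.0324 | 0.0304 |
| 0.3 | 0.358 | 0.452 | 0.892 | 0.0328 | 0.0292 |
| 0.4 | 0.450 | 0.561 | 0.828 | 0.0332 | 0.0275 |
| 0.5 | 0.542 | 0.668 | 0.745 | 0.0336 | 0.0250 |

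The reduction in standard error runs from 6% to 26%. Over the whole SD range the unadjusted standard error is 0.026 to 0.040. A one-standard-error baseline gap therefore moves the estimate by ρ, or about one third to two thirds, of its own standard error.

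**Step 5, sensitivity.** The slope b and the SE ratio depend on neither SD nor n. With the anticipated 20% drop-out (73 × 0.8, about 58 per arm) and SD 0.25, the standard error falls from 0.0363 to 0.0342 at r = 0.2 and from 0.0377 to 0.0280 at r = 0.5, so the proportions are unchanged. The correlation r decides the gain.

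**Costs.** The document gives no cost SD or correlation, so no figure can be derived.

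**The case against.** The strongest objection is that this is silence in a condensed article. A covariate list for a cost or QALY regression is often left to the full protocol or analysis plan, and a linear mixed model takes covariates readily. Adding baseline utility would be consistent with section 2.4.10 as it stands. Clustering is given as the reason for choosing mixed models, which is not the same as a complete list of model terms. This stands, and it is why the point is an improvement and not a defect.

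A reader might infer that the plan commits to an unadjusted analysis and will report a baseline gap as a treatment effect. The text does not support that: it neither names covariates nor excludes them. A reader might also infer that baseline costs are collected to no purpose. They could serve as a covariate or in the imputation model, whose variables the article does not list.

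Sections 2.4.8 and 2.4.9 show that adjustment is contemplated for the clinical outcomes. They do not settle the economic models, because section 2.4.10 does not invoke them and the rule they offer is discretionary. Whether to adjust the QALY difference should not be decided after the baseline comparison has been seen.

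It is also fair that the sizes rest on assumed values. Entry requires leg pain above 6 on the NPRS (section 2.2.1), which may narrow the spread of baseline utility and lower r. At r = 0.2-0.3 the standard error falls by only 6-11%.

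**Conclusion.** The point holds as a free improvement to the economic analysis. The document contains no error or contradiction here. Section 2.4.10 describes the models in some detail, ties them to clustering and names no baseline term. Run with nothing added, they give a QALY difference that is unbiased on average under randomization but, in the one trial that is run, carries part of any chance baseline gap and is less precise than the data allow.

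Under the stated assumptions the share carried is 27-54% and the avoidable part of the standard error is about 6-26%, with the low end plausible. A larger claim, that the QALY result would be biased or that a specific gain in power is being lost, goes beyond the documents: allocation is randomized, the trial is not powered on QALYs, and the correlation that decides the gain is not given. For costs the same reasoning gives a direction but no size.

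**What to change.** In section 2.4.10, state that:

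- the QALY model includes baseline EQ-5D-5L utility, and the cost models baseline cost, as covariates;
- this applies regardless of the baseline balance check in section 2.4.7;
- the models are fitted within each imputed data set and bootstrap sample, with the planned clustering level kept;
- the adjusted differences feed the ICER, the cost-effectiveness planes and the acceptability curves.

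The cost is a sentence or two and one added covariate in each model already planned. No further data, visits or patients are needed, because both values are already collected at baseline. If the full protocol or analysis plan already specifies this, a cross-reference is enough.

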## DISCUSSION

3

Prior to this study, only our pilot study has evaluated the effectiveness of a combination therapy (MDT and TESIs) in patients presenting with lumbar disc herniation (van Helvoirt et al., 2014). The pilot study indicated the importance of a multidisciplinary approach, which addresses the inflammatory and mechanical contributors to spine mediated pain, and has the potential to reduce the numbers of herniated disc surgery. However, the cost‐effectiveness of the combination therapy was not explored. The results of the pilot study should be interpreted with great caution because of lack of a control group.

The importance of this study is further emphasized by the fact that there are huge discrepancies in the treatment and management of lumbar disc herniation regionally and internationally (Weinstein et al., 2006). In addition, a lot of costs and burden to society have been associated with LRS (Health Council of the Netherlands, 1999). Therefore, the combination therapy may benefit not only individual patients but also society as a whole.

To our knowledge, this is the first randomized controlled trial investigating the effectiveness and cost‐effectiveness of the combination therapy in patients with LRS compared with usual care. Therefore, the present study aims to determine if a combination therapy, while being on the waiting list for a lumbar herniated disc surgery, is effective and cost‐effective compared with usual care among patients with an indication for a lumbar herniated disc surgery. Hence, this research will help bridge the knowledge gap in the treatment and management of patients with LRS.
